### Interventions

Surgical procedure, that is approach and extent of surgical excision as well as post-operative hand therapy, will not be standardised. Surgeons vary in their preference and skill for different procedures and it is difficult to standardise these. Immediate post-operative management including the use of plaster of Paris or thermoplastic resting splints, type of dressing and time to removal of sutures varies between surgeons and centres. Local standard protocols will be followed. For the purposes of this trial the intervention period commences at the first hand therapy appointment which is normally after suture removal (7–14 days after surgery). Hand therapy will be tailored to the patients presenting problems and needs and is aimed at reducing oedema, promoting wound healing and guiding post-surgical scarring, maximising finger range of movement and facilitating full return to functional use of the hand. This can be achieved through a wide range of modalities. The hand therapists who deliver the treatment will use a standard checklist to record the number of sessions each patient receives as well as the modalities and treatments received at each session.

#### Splint group

The use of a static night splint is standard practice in all 5 participating centres for the majority of patients, consequently the provision of the night splint in this trial does not constitute a new intervention. Therapists already have training and experience in manufacturing custom-made splints for DC and local protocols and procedures regarding choice of material and design will be followed. Splints will be static with no dynamic components. The principle of 'no tension' ([11,13]will be used. This involves placing the operated digits in maximum achievable extension without placing tension on the surgical wound. Any non-correctable contractures at the time of surgery will be accommodated in the splint.

Where splints are contra-indicated, for example due to post-surgical complications, the application of the splint is delayed. Patients allocated to the splint group will be asked to wear splints at night-time only for 6 months. They are given a simple splint diary in which they record on a weekly basis how many nights out of 7 they actually wore the splint and reasons for not doing so. The splint diary will be collected at the 3 months and 6 months follow-up visit by the research associates.

#### No splint group

Patients allocated to the no-splint group will receive hand therapy as described above only. During the early post-operative phase and especially where the surgical scar crosses the metacarpophalangeal (MCP) or interphalangeal (IP) joints patients may experience loss of extension due to the tendency of scar tissue to contract. Such a loss of finger extension may be temporary and also may respond to other treatment modalities such as active exercises, scar massage etc., however where this does not resolve within a week and exceeds an acceptable threshold patients will be given a splint. The criteria for such protocol deviations have been devised and agreed by all participating centre surgeons and therapists. The first hand therapy visit after surgery will be used to record baseline active extension at MCP and proximal interphalangeal (PIP) joints. On subsequent visits this is reassessed and if loss of extension compared to this baseline is greater than 20° at the PIP joint or greater than 30° at the MCP joint patients will be given a splint. Protocol deviations and reasons for these will be recorded.

### Outcomes

Surgical release of a Dupuytren's contracture is primarily designed to 'open up' the palm and restore finger extensibility and improve hand function. Past studies of splinting have reported outcomes in terms of total active extension and total active flexion as well as self-reported symptoms, function and disability.

The primary outcome measure is self-reported hand function and disability assessed by the Disabilities of Arm Shoulder and Hand Questionnaire (DASH)[14]. The DASH is a 30-item patient-reported questionnaire designed to measure, symptoms and physical function in patients with musculoskeletal disorders of the upper extremity. There is no disease-specific outcome instrument for Dupuytren's contracture and the validation of the DASH has been done on a wide range of patients including Dupuytren's contracture. Longitudinal construct validity has been assessed in patients including those with DC and the responsiveness assessed by effect size is moderate (ES = 0.5). It has good concurrent validity with the subscales of the SF-36 [15] and test-retest reliability has been found to be excellent (ICC = 0.96) [16].

Secondary outcomes are range of movement, patient satisfaction and recurrence. Range of movement for digits I to IV will be assessed using a Rolyan hyperextension finger goniometer and following a standardised protocol. Total active flexion (TAF) and total active extension (TAE) will be recorded by adding individual DIP, PIP and MCP joint scores. Intra-tester reliability of finger goniometry using a standardised protocol has been shown as acceptable [17] with a within-tester error of less than 5 degrees.

Patient satisfaction will be assessed at 6 and 12 months using an 11 point verbal rating scale (VRS) with the question: How satisfied are you with the overall result of the surgery now? A score of 0 means completely dissatisfied and 10 means completely satisfied.

Recurrence of contracture in the previously operated field [10] will be assessed only at 6 months and 12 months post surgery by MCP and PIP joint extension deficit.

Baseline data on socio-demographic variables (including age, gender, handedness, previous surgery and occupational status) will be collected at the pre-operative appointment together with RoM measurements and DASH questionnaire. A number of other measures will be obtained: patients allocated to the splint group will be asked to keep a splint diary to measure splint adherence. Frequency and type of treatment received by the hand therapists will be recorded.

#### Timing of outcome measures

Baseline assessment will occur at 4 to 8 weeks prior to surgery. Follow-up assessments at 3 months, 6 months and 1 year post-surgery as well as baseline assessment will be taken by the research associates employed on the trial. Patients will be visited at home in order to measure finger range of movement with a finger goniometer using a standardised protocol and collect the completed DASH Questionnaire which is posted out prior to the visit. At the 6 months and 12 months follow-up visit the verbal rating scale for satisfaction will also be administered and the presence or absence of recurrence in contracture (as distinct from scar or joint contracture) will be assessed. The patient completed splint dairy will also be collected at 3 months and 6 months and the patient asked to rate their overall adherence with splint wear as an average proportion out of 7 days.

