### Blinding

Due to the nature of this study, it is not possible to blind the patient or the treating therapist to the intervention received. The primary outcome measure is the patient-rated DASH and therefore blinded assessment is not possible. Secondary outcomes will be assessed by research associates who will not be blinded to the group allocation.

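### Satisfaction is collected by unblinded research associates at home visits although a self-completed form is already posted for the same visits, leaving a secondary outcome open to avoidable interviewer influence

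*Protocol article*

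**What the plan says.** All references are to the Protocol article.

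- **Status of the outcome (Outcomes):** "Secondary outcomes are range of movement, patient satisfaction and recurrence". Satisfaction also appears in the trial objective.
- **Instrument (Outcomes):** "Patient satisfaction will be assessed at 6 and 12 months using an 11 point verbal rating scale (VRS) with the question". The question concerns the overall result of the operation, scored from 0 to 10.
- **Collection (Timing of outcome measures):** "At the 6 months and 12 months follow-up visit the verbal rating scale for satisfaction will also be administered".
- **Who and where (Timing of outcome measures):** follow-up assessments "as well as baseline assessment will be taken by the research associates employed on the trial", and "Patients will be visited at home in order to measure finger range of movement".
- **Assessor blinding (Blinding):** "Secondary outcomes will be assessed by research associates who will not be blinded to the group allocation".
- **DASH at the same visits (Timing of outcome measures):** the associates "collect the completed DASH Questionnaire which is posted out prior to the visit".
- **Adherence (Timing of outcome measures):** at 3 and 6 months the splint diary is collected and "the patient asked to rate their overall adherence with splint wear as an average proportion out of 7 days". The Splint group section gives the diary to patients allocated a splint.

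**The concern.** Satisfaction is one subjective rating with no objective anchor. The plan has it given in person by someone who knows which arm the patient is in. Tone, prompting, or a patient's wish to please a visitor who knows about the splint could move the answer in one arm more than in the other. A shift of that kind goes straight into the treatment comparison. The planned adjustment for hospital and type of surgery cannot remove it, because it runs with allocation.

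The Blinding section explains why patients, therapists and the patient-rated DASH cannot be blinded. For the associates it states the lack of blinding without a reason. Range of movement needs a visitor with a goniometer, but a 0-10 satisfaction rating does not. At stake is the credibility of one secondary comparison.

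**Working it through.** The plan gives no figure for satisfaction, so there is nothing to reproduce. The check has two parts.

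**1. The sections side by side**

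| Feature | DASH | Satisfaction |
|---|---|---|
| Source of the answer | Patient | Patient |
| How collected | Posted, completed before the visit, then collected | Verbal scale, administered at the visit |
| Unblinded associate involved in obtaining the answer | No | Yes |
| Stated need for an interviewer | None | None |
| Stated safeguard | Self-completion | None |

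That the question is asked and answered aloud is an inference from a verbal scale being administered at a visit. It is the natural reading, but the text does not say so outright.

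Content of the visits:

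- **6 months:** satisfaction, range of movement, recurrence and DASH collection in both arms, plus the diary and adherence rating, which apply to the splint arm. The order of questions is not fixed.
- **12 months:** the same without the diary or adherence rating. The content of the visit does not differ by arm, and only the associate's knowledge of allocation remains.

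**2. Illustration of size**

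Inputs:

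- n = 51 per arm, from the Sample size section (the number needed before allowance for loss).
- SD of satisfaction: not in the document, assumed 2 to 3 points.
- Shift b between arms caused by the interviewer: not in the document, assumed 0.25 or 0.5 points.
- Test: two-sided 5%, assumed because the article states no significance level. No true difference.

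Formulas: SE = SD × √(2/n), and false-positive rate = Φ(b/SE − 1.96) + Φ(−b/SE − 1.96).

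- SD 2: SE = 2 × √(2/51) = 0.396. For b = 0.5, b/SE = 1.26 and the rate is 0.243.
- SD 2.5: SE = 2.5 × √(2/51) = 0.495. For b = 0.5, b/SE = 1.01 and the rate is 0.173.
- SD 3: SE = 3 × √(2/51) = 0.594. For b = 0.5, b/SE = 0.84 and the rate is 0.134.
- For b = 0.25 the rates are 0.097 (SD 2), 0.080 (SD 2.5) and 0.071 (SD 3).

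So a half-point shift would give about 24% to 13%, and a quarter-point shift about 10% to 7%. These figures show how sensitive the comparison would be if a shift occurred. They are no evidence that one would occur.

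**The case against.** The strongest case against has five parts.

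- **The item is about surgery, and both arms have surgery.** The associates neither operate nor make splints, so nothing in the article shows why courtesy towards them should differ by arm. This stands to the extent that a differential effect is possible but not shown. Even so, the score is compared between arms as an effect of splinting, by staff who know the arm.
- **Patients know their own allocation.** This stands in full. Posting the question would leave their expectation in place. The point covers only the added influence of the interviewer.
- **The lack of blinding is disclosed.** It is, but disclosure does not remove the bias, and here a way round it is already in use for the DASH.
- **The mode may be an operational detail.** A condensed article may omit scripts or a printed card that the patient marks. That is possible. However, the article does fix the type of scale, the occasion and the unblinded assessor, and the point concerns those stated choices.
- **The illustration is circular.** Any assumed bias of about one standard error yields a similar inflation for any outcome. This stands, and the figures serve as illustration only.

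A reader might infer more than the documents support:

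- *That blinding the associate would not help.* The differential harm depends largely on the associate knowing the arm. Influence common to both arms cancels in the comparison, so blinding would help.
- *That the adherence questions contaminate the one-year result.* They are described at 3 and 6 months only.
- *That differences between associates covering different centres bias the comparison.* The article does not say how associates are assigned. Randomization is stratified by hospital and hospital is in the model, so a shift at centre level would be balanced and adjusted for.

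**Conclusion.** The point holds as a minor, cheaply avoidable weakness in one secondary outcome. The plan collects satisfaction through research associates who know the allocation, states neither a safeguard nor a need for an interviewer, and already posts a self-completed form for the same visits. The difference in visit content between arms applies at 6 months and not at 12.

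The size of any bias is unknown. The range of about 24% to 13% for a half-point shift rests wholly on the assumed SD of 2 to 3, the assumed shift, 51 per arm and an assumed two-sided 5% test.

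It would be wrong to conclude that the trial's main result is at risk. The DASH is completed before the visit, and its analysis is untouched.

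**What to change.** Print the same 0-10 satisfaction question, in the same words, on the sheet posted with the DASH at 6 and 12 months, for the patient to complete before the visit. The associate only checks that it has been answered. If it is blank, the patient completes it in writing at the visit, before any adherence questions. Describe the item in the Outcomes and Timing of outcome measures sections as self-completed.

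The cost is one line on a sheet already posted, and the small downside is a few blanks. No extra visit, change of sample size or change of analysis is needed.

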### Blinding

Due to the nature of this study, it is not possible to blind the patient or the treating therapist to the intervention received. The primary outcome measure is the patient-rated DASH and therefore blinded assessment is not possible. Secondary outcomes will be assessed by research associates who will not be blinded to the group allocation.

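### Range of movement and recurrence are assessed by unblinded research associates who collect a splint-arm-only diary at the 3- and 6-month visits, exposing two secondary outcomes to partly avoidable detection bias

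*Protocol article*

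**What the plan says.** All references are to the protocol article.

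- **Blinding.** Patients and treating therapists cannot be blinded. For the primary outcome: "The primary outcome measure is the patient-rated DASH and therefore blinded assessment is not possible". For the rest: "Secondary outcomes will be assessed by research associates who will not be blinded to the group allocation". No reason is attached to that last sentence.
- **Timing of outcome measures.** Follow-up at 3 months, 6 months and 1 year "as well as baseline assessment will be taken by the research associates employed on the trial". On range of movement: "Patients will be visited at home in order to measure finger range of movement with a finger goniometer using a standardised protocol". At 6 and 12 months "the presence or absence of recurrence in contracture (as distinct from scar or joint contracture) will be assessed".
- **Splint group.** "The splint diary will be collected at the 3 months and 6 months follow-up visit by the research associates". The Timing section repeats this and adds the rating: "The patient completed splint dairy will also be collected at 3 months and 6 months and the patient asked to rate their overall adherence".
- **Outcomes.** The diary belongs to one arm: "patients allocated to the splint group will be asked to keep a splint diary to measure splint adherence".
- **Randomization.** The treating hand therapists obtain the allocation by telephone at about the first post-operative therapy appointment.
- **Objectives of the trial.** Total active movement and recurrence at one year are both named.

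**The concern.** Unblinded patients and therapists are unavoidable in a splinting trial. Unblinded assessors are a separate choice, and the article makes it without a reason that fits the outcomes concerned. Reading a joint angle does not require knowing the arm, and neither does deciding whether an extension deficit is recurrent disease or scar.

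The visit schedule adds to the exposure. A diary that exists in one arm only is handed to the person holding the goniometer.

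At stake is how far two secondary outcomes can be trusted. The DASH and satisfaction are ratings by patients who know their group, so movement and recurrence are the outcomes for which a blinded assessor could remove some of the bias. Expectation could run either way: splinting is standard for most patients at all five centres, while the Background describes the evidence as conflicting. The planned estimating equations and Fisher's exact test cannot correct readings that lean by arm, so any remedy has to come before data collection.

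**Working it through.** The article gives no figure to reproduce on this point. The check sets the sections side by side and then illustrates the sensitivity of the two outcomes.

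**1. Does a stated reason cover these outcomes?**

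| Outcome | Source of the value | Reason given for no blinding |
|---|---|---|
| DASH (primary) | Patient | Patient-rated |
| Satisfaction | Patient, asked aloud | None specific, but the rater is an unblinded patient |
| Range of movement | Associate, goniometer | None |
| Recurrence | Associate, from MCP and PIP extension deficit, separated from scar or joint contracture | None |

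**2. Must the associates know the arm?** Therapists obtain the allocation (Randomization). Associates make the assessment visits (Timing). No assessment task needs the allocation. The article does not say whether associates are also told it by another route.

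**3. When do the documented visit tasks disclose the arm?**

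| Visit | Goniometry | Recurrence | Diary and adherence rating |
|---|---|---|---|
| 3 months | yes | no | yes |
| 6 months | yes | yes | yes |
| 12 months | yes | yes | no |

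Disclosure through the diary is documented at 3 and 6 months. At 12 months it could act only by carry-over, if the same associate returns.

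**4. Arithmetic illustrations.** Total active extension sums the DIP, PIP and MCP joints. An assumed lean of 2 degrees per joint in one direction gives 3 × 2 = 6 degrees. With 51 per arm (Sample size), 3 borderline recurrences called one way in one arm and 3 the other way in the other arm give 3/51 + 3/51 = 6/51 = 11.8 percentage points. Both leans are assumed.

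**5. Would shifts of this order change a test?** Assumptions: no true effect, 51 per arm, two-sided 5% level (the article states none).

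*Range of movement.* The article gives no SD, so 15 to 40 degrees is assumed, with one value per patient. For a between-arm reading difference b: SE = SD × √(2/51), λ = b/SE, and the rejection rate is 1 − Φ(1.96 − λ) + Φ(−1.96 − λ). For SD 15 and b = 5: SE = 15 × 0.198 = 2.97, λ = 1.68, rate 39.1%.

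| b (degrees) | SD 15 | SD 20 | SD 30 | SD 40 |
|---|---|---|---|---|
| 2.5 | 13.4% | 9.7% | 7.1% | 6.1% |
| 5 | 39.1% | 24.3% | 13.4% | 9.7% |

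*Recurrence.* The article gives no rate, so 10% to 30% is assumed. Rejection rates of Fisher's exact test by enumeration:

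| Differential misclassification | Rate 10% | Rate 20% | Rate 30% |
|---|---|---|---|
| 0 points | 1.8% | 2.9% | 3.1% |
| 5 points | 6.3% | 6.1% | 5.6% |
| 10 points | 20.1% | 16.0% | 13.7% |

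Small leans do little. Leans of 5 degrees or 10 points matter, and for movement the effect depends heavily on the SD.

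**The case against.** The case for leaving the plan alone has several good parts.

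- **It is disclosed and secondary.** The article states the lack of blinding openly, contradicts nothing, and rests its sample size on the DASH, which is posted to patients before the visit. This stands and limits the severity. A reader might infer that the main result is compromised; the article does not support that, since blinding the associates would leave the DASH as it is.
- **The full protocol may give a reason.** Possible, because an article condenses. But the choice itself is stated here, and the reasons that were printed do not reach these outcomes.
- **Safeguards exist.** Goniometry follows a standardised protocol, and recurrence is based on extension deficit. Both are partial. The cited within-tester error of less than 5 degrees describes repeatability; it neither shows nor excludes a lean by arm.
- **Movement is not a fully objective check.** Flexion and extension are active, so they depend on the effort of a patient who knows the arm. This stands: a blinded assessor removes only part of the bias.
- **Home visits leak.** Patients may mention or show the splint whatever happens to the diary. This also stands, and it makes blinding imperfect without making it pointless.
- **Cost is unknown.** A reader might infer that blinding needs no extra staff. That is plausible, since associates and therapists are described separately and a trial co-ordinator already handles postal packs, but the article gives no staffing figures.

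**Conclusion.** The point holds as a design weakness of moderate severity. Two secondary outcomes named in the one-year objective are assessed unblinded without an applicable reason, and at 3 and 6 months the visit tasks themselves disclose the arm. The resulting detection bias is partly avoidable and cannot be repaired in the analysis.

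Its size is unknown. The 6-degree and 11.8-point figures, and the error rates in the tables, show what assumed leans would do. They are not estimates of bias in this trial, because the article supplies neither a range-of-movement SD nor a recurrence rate.

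Two further inferences are tempting and go too far. The first is that the visits reveal the arm throughout follow-up: the diary does so only at 3 and 6 months, although the Blinding section treats the associates as unblinded without limit. The second is that any movement or recurrence result would be uninterpretable: the standardised measurement gives some protection.

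**What to change.** In the Blinding and Timing of outcome measures sections:

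1. State that research associates are not told the allocation.
2. Ask patients before each visit to put any splint out of sight and not to mention their group.
3. Have goniometry and the recurrence assessment completed and recorded before any other visit task.
4. Have the splint diary and adherence rating returned sealed, or by post to the trial co-ordinator, so that the associate does not handle them openly.
5. Have the associate record a guess of the allocation after measuring, at 12 months in particular, and report it.

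Leave the satisfaction item where it is: the patient rates it, and moving it to paper would change a verbal scale. Passing diary collection to the therapists is not advised either, because the article does not show that patients still attend therapy at 3 or 6 months.

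The cost is revised wording, reply envelopes and one extra item on the visit form. Some diaries may be lost, which weakens the adherence data, and some patients will still reveal their group. Sample size and trial treatment do not change.
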